### Study design

The study design is a randomised controlled trial. A scheme of the study is shown in Figure 1.

**Figure 1 F1:**
[figure not shown]
**Randomised controlled trial design**.

The patients will be classified into five levels according to the Gross Motor Function Classification System (GMFCS) and subsequently randomly divided into two treatment groups.

1.- Treatment Group with hippotherapy simulator switched on.

2.- Treatment Group with hippotherapy simulator switched off (without rhythmic movement).

The randomising will be centralised and generated by computer according to stratified groups to ensure a similar distribution of the possible confounding variables in both groups. The assignation sequence will be concealed.

Ten treatment sessions (one weekly) will be given in each modality, in which the children will do different activities proposed by the physiotherapist according to their motor possibilities.

In the treatment sessions with the hippotherapy simulator switched on, the children will maintain the sitting position for 15 minutes on the simulator, with an active extension of the trunk, stabilization of the pelvis and abduction of hips while the simulator produces a rhythmic and repetitive movement that is similar to a walking horse. In the treatment sessions with the simulator switched off (without providing the rhythmic movement), the children will maintain the active extension of the trunk, stabilization of the pelvis and abduction of hips but they won't benefit from the rhythmic effects produced by the hippotherapy simulator. That is, the children who sit on the simulator that is switched off will receive the same treatment except that they won't receive rhythmic movement from the simulator (it would be similar to sitting on a barrel or another device in which they maintain this sitting position, similar to other studies published^7^).

Children not included in the group with the simulator switched on will be offered the possibility to receive ten more treatments with the simulator switched on once the research has concluded.

### Study variables

The hippotherapy simulator used for this study is "Core Trainer Exercise Equipment, JOBA" produced by Matshuita (Panasonic), and allows working at 9 speeds and 3 predefined programmes (basic conditioning, waist, hips).

This simulator was designed to be used in fitness centres. To make it easier to use the system offers three automated training routines:

WORKOUT (Side-To-Side)

WAIST (Forward Tilt)

HIPS (Backward Tilt)

These training routines can automatically modify the speed and tilt of each one of the training sub phases

When planning a work session with the JOBA commercial Simulator, the time, tilt and speed adjustment allows for unequivocally defining the test parameters. Therefore using the same Simulator and knowing these parameters, the repeatability of the test is totally guaranteed. In the case of our study, we have listed the exact programme that was used, which is Side-To-Side WORKOUT.

The study variables will be measured with the instruments showed in table 1 (see table 1).

**Table 1 T1:** Study variables and instruments for measurement.

STUDY VARIABLES	INSTRUMENTS
Sitting balance	SAS (Sitting Assessment Scale) [21]

Muscular activity in hip adductors	Surface Electromyography (EMG)

Hip abduction range of motion	Electronic inclinometer and traditional goniometer

Gross motor function	Gross Motor Function Measure (GMFM)

There are four outcome variables:

- Sitting balance

- Measurement of hip abduction range of motion

- Electromyographic activity in adductors

- Global motor development

The outcome variables will be measured at three different times during the research. A first measurement will be made at the beginning of the study, a second one when the ten treatment sessions have concluded, and a third measurement after the 3-month follow-up period. Moreover, two of these outcome variables (hip abduction range of motion and Electromyographic activity in adductors) will also be measured before and after each treatment session.

Control of confounding variables (independent variables) will be carried out on each and everyone of the outcome variables studied. The confounding variables considered to be studied will be those listed below:

- Sociodemographic variables: sex, age and physical activity.

- Clinical variables: oral anti-spascity medication treatment, other medical treatments that could interfere with the hippotherapy treatment (antiepileptic drugs, etc.), medical diagnosis, previous experience in hippotherapy, off-trial hippotherapy treatments, surgical interventions, botulinum toxin injections and use of ortheses.

A questionnaire will be completed at the beginning of the study that collects the confounding variables previously described. Monitoring will be carried out throughout the duration of the study.

Data collection and analysis: all measurements will be carried out by a specially trained blind method consultant. It is a triple blind trial because patients, researchers and statisticians were unaware of the group the subjects of the study belonged to. To ensure standardization quality of the consultants, an inter-examiner agreement will be worked out at the start of the study.

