### Sample

The subjects of the study are children between 4 and 18 years old with CP, who attend schools run by the Education Department of the Government of Aragon (Spain) and whose tutors have signed an informed consent form.

Regarding the sample size, a calculation of statistical power was made previous to the study. The calculation of statistical power was based on a non-published introductory research of the effects of a commercialized hippotherapy simulator for cerebral palsy children. In this study, an improvement of 60% was obtained in cases against 10% of improvement in controls, so improvement probability is considered to be at least double in cases than in controls (odd ratio of 2). In order to assure a power of 0.90 the sample should be 17 in every group (total sample 34). The sample size was considered to be 10% greater due to possible drop-outs (37-38 children).

All CP children that fit the inclusion criteria were selected to participate (37 children). In this study it is hoped to assign at least 18 subjects randomly to each experimental condition.

In cases where tutors or children do not wish to participate, the following variables will be recorded: Sex, age, level of Gross Motor Function Classification System and cause to refuse to participate.

The exclusion criteria are as follows:

- Children who have undergone selective dorsal rhizotomy

- Acute convulsions not controlled by medication

- Allergy to electrode adhesives

- Visual impairment not corrected with glasses

- Those circumstances or associated illnesses that in the judgment of the researcher might interfere with the results or be detrimental to the children.

- Inability to attend intervention sessions or refusal to participate.

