### Statistical analysis

The data will be entered and analyzed with SPSS 14.0, and the following statistical procedure will be undertaken:

1. Descriptive analysis of defined variables.

2. Mean comparison tests for quantitative variables and comparison of proportions for qualitative data, among independent variables to check the comparability of the groups.

3. Mean comparison tests for each outcome variable according to the treatment group (differences pre-post treatment in both treatment groups as well as differences between them)

4. Multivariate analysis to determine the influence of independent variables in the evolution of each outcome variable.

A descriptive analysis of drop outs will also be made in order to determine if there are correlating patterns.

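### Hip abduction range and adductor EMG appear to have two untreated readings; averaging them as the baseline would gain some precision at almost no cost

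*Protocol article*

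**What the plan says.** In the protocol article, Study variables, the four outcomes are measured at three times: "A first measurement will be made at the beginning of the study, a second one when the ten treatment sessions have concluded", and a third after the 3-month follow-up. The next sentence says that two of the four, hip abduction range and adductor EMG, "will also be measured before and after each treatment session". The text under Figure 1 sets the number of sessions: "Ten treatment sessions (one weekly) will be given in each modality".

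Item 3 of Statistical analysis plans mean comparisons for each outcome by treatment group, described as "differences pre-post treatment in both treatment groups as well as differences between them". It does not define which reading or readings supply the *pre* value, and it does not mention the session readings.

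**The concern.** The session readings are introduced as an addition to the three study measurements. For hip abduction range and adductor EMG, the reading before session 1 is then a second measurement of a child who has not yet been treated. The natural *pre* value in item 3 is the first of the three study measurements. If only that one is used, all of its measurement error passes into the child's change score, while a second reading of the same untreated state is left out of the baseline.

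At stake is the width of the interval for the effect of the simulator's movement on two of the four outcomes. According to the Sample section, all 37 eligible children were selected, so extra precision has to come from the analysis and not from more recruitment.

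**Working it through.** **The plan's own figure.** The Sample section bases the size on improvement rates ("an improvement of 60% was obtained in cases against 10% of improvement in controls") and concludes: "In order to assure a power of 0.90 the sample should be 17 in every group (total sample 34"). With two-sided alpha 0.05 (assumed, as the article does not state it) and no continuity correction:

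n = [1.960 × √(2 × 0.35 × 0.65) + 1.282 × √(0.6 × 0.4 + 0.1 × 0.9)]² / 0.5² = (1.322 + 0.736)² / 0.25 ≈ 16.9, so 17 per group.

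Power at 17 per group is 0.901. The figure reproduces, but it does not bear on this point, because it is a calculation for a yes/no improvement and uses no baseline reading. It serves below only as a group size.

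**Inputs for the baseline question.**
- From the article: one first study measurement, one reading before session 1 (if separate), one post-treatment measurement.
- Assumed, because the article gives no SD, reliability or correlation: equal variances (set to 1); correlation rho between the two untreated readings, 0.7 to 0.95; the same correlation r between each untreated reading and the post-treatment reading, 0.5 to 0.9, with r no larger than rho.

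**Formulas.**
- Change score, one baseline reading: 2(1 − r).
- Change score, mean of two: 1 + (1 + rho)/2 − 2r = 1.5 + rho/2 − 2r. The relative reduction is (1 − rho) / [4(1 − r)].
- Baseline as covariate, one reading: residual variance 1 − r².
- Baseline as covariate, mean of two: 1 − 2r²/(1 + rho).

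**Results.**

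| rho | r | Change score, one → two | Fall | Adjusted, one → two | Fall |
|---|---|---|---|---|---|
| 0.70 | 0.50 | 1.000 → 0.850 | 15.0% | 0.750 → 0.706 | 5.9% |
| 0.70 | 0.70 | 0.600 → 0.450 | 25.0% | 0.510 → 0.424 | 17.0% |
| 0.80 | 0.70 | 0.600 → 0.500 | 16.7% | 0.510 → 0.456 | 10.7% |
| 0.90 | 0.50 | 1.000 → 0.950 | 5.0% | 0.750 → 0.737 | 1.8% |
| 0.90 | 0.80 | 0.400 → 0.350 | 12.5% | 0.360 → 0.326 | 9.4% |
| 0.90 | 0.90 | 0.200 → 0.150 | 25.0% | 0.190 → 0.147 | 22.4% |
| 0.95 | 0.50 | 1.000 → 0.975 | 2.5% | 0.750 → 0.744 | 0.9% |
| 0.95 | 0.70 | 0.600 → 0.575 | 4.2% | 0.510 → 0.497 | 2.5% |
| 0.95 | 0.90 | 0.200 → 0.175 | 12.5% | 0.190 → 0.169 | 10.9% |

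Over the grid, the standard error is multiplied by 0.987 to 0.866 for the change score and by 0.996 to 0.881 for the adjusted analysis.

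In power terms, take an effect that one baseline reading detects with 80% power at 17 per group. With two readings, power is 81.0% to 89.9% for the change score and 80.3% to 88.9% for the adjusted analysis. At rho 0.8 and r 0.7 it is 86.6% and 84.2%.

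The 25% figure is an upper edge. It needs rho = r, that is, two untreated readings no more alike than readings on either side of ten weekly sessions. If the first measurement and the reading before session 1 are the same reading, rho is 1 and the gain is zero.

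**The case against.** **A single baseline is not stated.** A reader might infer that the plan commits to one baseline reading and discards the other. The article does not say so: *pre* is undefined, no reading is excluded, and the multivariate step in item 4 could draw on the session readings. The choice may also sit in an analysis plan that is not shown. This stands, and it is why the point is not an error or a contradiction. What remains is that the article states both the schedule and the pre-post comparison, and an improvement to that comparison is open.

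**The two readings may not be separate.** The article gives no interval between the start of the study and session 1. The wording points to an extra reading but does not settle it, so the fix has to be conditional.

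**The readings may not be interchangeable.** Hip abduction is listed with both an electronic inclinometer and a traditional goniometer, and the article does not say which is used at sessions. This is largely met: Table 1 names the instruments for the study variables without separating occasions, and all measurements go to a trained blinded assessor. A condition on instrument and procedure covers the rest.

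**Two stronger readings fail.** One might argue that the reading before session 1 is also protected from knowledge of allocation. It follows randomisation, and the article does not say when families or the treating physiotherapist learn whether the simulator will move. One might also turn the gain into a fixed number of extra children. That needs one particular pair of correlations, and the documents supply none.

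**Conclusion.** The point holds as a small efficiency improvement to item 3 for two of the four outcomes. The direction is secure if the two untreated readings are separate and imperfectly correlated, with equal variances and equal correlations with the post-treatment value; under those assumptions the averaged baseline cannot do worse than a single reading. The size is not secure. It may be negligible where the two readings agree very closely but track the post-treatment value loosely, and the ranges in the working rest wholly on assumed correlations. Nothing here undermines the validity of the planned comparison, since a single baseline reading is ordinary practice.

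**What to change.** Add one sentence to item 3 of Statistical analysis. For hip abduction range and adductor EMG, where the first study measurement and the reading before session 1 are separate readings taken with the same instrument and procedure, the baseline in the between-group comparison is their mean, in both arms. If one is missing, the available one is used. Preferably the mean enters as a covariate.

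It would help to state at the same time whether the two readings are in fact separate. If they are not, the sentence is not needed.

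The cost is one or two sentences of text. If the readings are separate, both are already scheduled, so no visit, measurement or staff time is added.

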**Methods/Design:**

The study is a randomised controlled trial. It will be carried out with a sample of 37 children with cerebral palsy divided into two treatment groups. Eligible participants will be randomly allocated to receive either (a) Treatment Group with hippotherapy simulator, maintaining sitting posture, with legs in abduction and rhythmic movement of the simulator or (b) Treatment Group maintaining sitting posture, with legs in abduction and without rhythmic movement of the simulator. Data collection and analysis: all measurements will be carried out by a specially trained blind assessor. To ensure standardization quality of the assessors, an inter-examiner agreement will be worked out at the start of the study. The trial is funded by the Department of Research, Innovation and Development of the Regional Government of Aragon (Official Bulletin of Aragon 23 July 2007), project number PM059/2007.

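### The triple-blind claim cannot hold for children or treating physiotherapists, because the arms differ only in whether the simulator moves; only the outcome assessor and the statistician can be blind

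*Protocol article*

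**What the plan says.** Under Study variables, in the paragraph on data collection and analysis, the protocol article says: "It is a triple blind trial because patients, researchers and statisticians were unaware of the group the subjects of the study belonged to". The sentence before it says that "all measurements will be carried out by a specially trained blind method consultant". The abstract (Methods/Design) makes only the narrower claim that "all measurements will be carried out by a specially trained blind assessor" and does not use the triple-blind label.

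The arms are set out under Study design, after Figure 1: "Treatment Group with hippotherapy simulator switched on" and "Treatment Group with hippotherapy simulator switched off (without rhythmic movement". The same section says that switched-off children "will receive the same treatment except that they won't receive rhythmic movement from the simulator", and compares their condition to sitting on a static support such as a barrel. Each arm has ten weekly sessions, and the switched-on sessions are described as 15 minutes on the simulator. A physiotherapist proposes the activities. The allocation sequence is to be concealed.

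All four outcomes are measured at baseline, after the ten sessions and at 3-month follow-up. In addition, hip abduction range and adductor EMG "will also be measured before and after each treatment session".

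**The concern.** Blinding means not knowing which arm a child is in. Here the arm is defined by something the child feels and the therapist watches, so the document claims a property its own design rules out for two kinds of people: those treated and those treating.

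What is at stake is how a positive result will be read. The SAS and the GMFM assess what a child does, so effort and encouragement can move the scores. The sessions ask the child for active trunk extension, which a therapist's enthusiasm can also affect. Families who know the arm may change physical activity or seek hippotherapy outside the trial; the protocol lists both among its confounders. A blinded assessor scores fairly what the child does on the day, but cannot undo differences in effort or outside treatment that came from knowing the arm. A reader told that the trial is triple blind would wrongly treat those explanations as excluded.

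**Working it through.** No figure in the protocol bears on this point, so the check sets the statements side by side and takes each party in turn.

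**Inputs**
- Parties claimed to be unaware: patients, researchers, statisticians (Study variables).
- Sole difference between arms: rhythmic movement of the simulator (Study design).
- Exposure: ten sessions of 15 minutes, as described for the switched-on arm; the switched-off arm is said to receive the same apart from movement (Study design).
- Sham motion or masking of movement: none described.
- Measurement: all by a blind assessor (abstract; Study variables).

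**Party by party**
1. *Children.* Each child sits on the device for 10 × 15 = 150 minutes in total if all sessions are attended. Whether it moves is directly felt. As group membership is exactly movement or no movement, the child cannot be unaware of it. The claim fails.
2. *Physiotherapists delivering sessions.* They propose activities while the child is on a moving or a still device. The claim fails for them if they are among the researchers meant.
3. *Families.* The sentence does not name them. That they will learn the arm from the child or by watching is a reasonable inference, not a statement in the document.
4. *Outcome assessor.* Nothing in the design prevents blinding, and both the abstract and Study variables provide for it. The claim is feasible.
5. *Statistician.* Coded groups make this feasible. The claim can stand.

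**Does concealment repair it?** No. Concealing the sequence protects the moment of assignment. It does nothing once the child is on the device.

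**How often assessor blinding is tested.** Two measurement occasions per session × 10 sessions = 20 occasions per child for hip range and EMG, besides the three main assessments. With 37 children and full attendance that is 37 × 20 = 740 occasions. The article does not say how the assessor stays unaware on them. This is a risk to manage, not evidence that blinding is lost.

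**The case against.** The strongest defence has four parts.

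- *Researchers may mean the people collecting data.* The sentence sits in a paragraph on data collection, directly after the one on the assessor, and treating staff are elsewhere called the physiotherapist. On that reading only one of the three named parties fails, not two. This is a fair reading, but the sentence does not state it, and the claim about patients fails either way.
- *Children may feel the movement without knowing which condition is under test.* That may be so for some in a sample aged 4 to 18 across five motor-function levels. But the document claims unawareness of the group, not of the hypothesis.
- *Important protection remains.* This stands. A reader might infer that the trial has no protection from bias. The documents do not support that: assessor and statistician blinding are stated, feasible, and guard against detection and analysis bias.
- *The design cannot blind children anyway, so only reporting changes.* Also true, but the correction changes what a result can be said to show.

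Four further inferences should not be drawn:
- The offer of switched-on sessions to the other arm ("Children not included in the group with the simulator switched on will be offered the possibility to receive ten more treatments") comes only after the research has ended. Nothing says that families hear of it earlier, so it does not show that any assessment is unblinded.
- The article gives no location for the per-session measurements, so it cannot be said that they are taken beside the device.
- Activities are tailored to motor ability under one rule in both arms. This does not contradict the statement that the arms differ only in movement.
- Treating per-session data as exploratory is a preference. All measurements are already assigned to the blind assessor, so nothing in the text requires it.

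**Conclusion.** The point holds: the triple-blind statement is wrong as written. Blinding is impossible for every child in both arms and for every physiotherapist delivering sessions. It remains possible for the outcome assessor and the statistician.

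The size of any resulting bias cannot be derived from the document, and none is claimed here. The practical effect is on interpretation: for the SAS and the GMFM, performance bias and co-intervention cannot be treated as excluded by design.

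The conclusion assumes that the switched-on device moves perceptibly and that no sham motion is used; the arm descriptions support both. It does not depend on how the word researchers is read, since the patient part of the claim fails alone. Randomisation, sample size and analysis are untouched.

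**What to change.** 1. Under Study variables, replace the triple-blind sentence with one saying that the outcome assessor and the statistician are blinded to group, and that children, families and treating physiotherapists are not. This brings the text into line with the abstract.
2. Add that between-group differences on the SAS and the GMFM will be interpreted as open to performance bias and co-intervention.
3. State that the blinded assessor stays out of the treatment sessions, including when taking hip range and EMG measurements around each one.

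The cost is some rewording, a weaker blinding claim, and a small logistic rule for an assessor who is already in place. No change to the arms, outcomes, sample size or analysis is needed.
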